## Abstract

**Background:**

Depressive disorders and problematic drinking often co-occur, also among young adults. These co-occurring conditions are associated with various negative health outcomes compared to both conditions alone. Early intervention by addressing alcohol use and depressive symptoms simultaneously in the same treatment might improve both conditions. However, evidence on the (cost-) effectiveness of digital combined depression and alcohol interventions for young adults is currently insufficient. We therefore developed an add-on digital alcohol moderation adherence-focussed guided intervention to complement treatment as usual (TAU) for depressive disorders. The digital intervention is a web-app, including 6 modules based on motivational interviewing and cognitive behavioural therapy. This study aims to evaluate the (cost-)effectiveness of a digital alcohol moderation intervention + TAU compared to TAU on alcohol and depression outcomes among young adults with co-occurring depressive disorders and problematic alcohol use.

**Methods:**

One hundred fifty-six participants, aged 18–35 years, with problematic alcohol use and a diagnosed depressive disorder will participate in a pragmatic multicentre two-arm randomized controlled trial. Problematic alcohol use is operationalised as scoring ≥5 for women and ≥ 8 for men on the Alcohol Use Disorder Identification Test (AUDIT). Participants will be randomized to either the experimental group (digital alcohol intervention + TAU) or control group (TAU only). Participants will be recruited at three Dutch mental health care centres and through social media. Assessments take place at baseline and after 3, 6 and 12 months post-randomization. The primary outcome is treatment response at 6-month follow-up, operationalized as a composite score that combines alcohol use and depression measures and indicates whether treatment has been successful or not. Secondary outcomes are depressive symptoms and alcohol use (i.e. number of weekly standard drinks and AUDIT score). An economic evaluation will be conducted alongside the trial.

**Discussion:**

This study evaluates the (cost-) effectiveness of an add-on digital alcohol moderation intervention for young adults who are in treatment for depressive disorders. If proven effective, the digital intervention could be implemented in mental health care and improve treatment for people with co-occurring depressive disorders and problematic alcohol use.

**Trial registration:**

Pre-registered on October 29, 2019 in The Netherlands Trial Register (NL8122).

## Background

Depressive disorders are common among adolescents, young adults and students, with lifetime prevalence rates up to 11–15, 27 and 21%, respectively [1–4]. Its onset is often in young adulthood and is associated with various adverse outcomes in mental health, education and employment in later adult life [1, 2, 5–8]. Alcohol use disorders (AUD) and other forms of problematic alcohol use, such as non-clinical levels of hazardous drinking, often co-occur with depressive disorders [9, 10]. Among young adults, lifetime prevalence of co-occurring depressive disorders and problem drinking is estimated to be up to 20% [11]. Co-occurring depressive disorders and problematic alcohol use are associated with higher risk of developing severe AUD, suicide attempts and greater disease burden and with lower life satisfaction and functioning compared to both conditions alone [11–13]. Considering these negative consequences in both current and later adult life, it is of great importance to intervene early among young adults who experience both concurrent conditions. By addressing alcohol use and depressive symptoms simultaneously in the same treatment setting, improvements may be reached in both.

Psychological treatment for co-occurring depressive disorders and problematic alcohol use often includes elements of motivational interviewing (MI) and cognitive behavioural therapy (CBT). Both treatment techniques have been found to be effective in reducing either problematic alcohol use [14–16] or depressive symptoms [17] among young people. In addition, two literature reviews have found MI/CBT-based treatments, often face-to-face delivered, to be effective in reducing both alcohol use and depressive symptoms simultaneously among people with co-occurring depression and problematic alcohol use [18, 19]. However, implementation of face-to-face delivered psychological treatment is often challenged by high costs and limitations in scalability. Contrary, digital-delivered treatment might overcome some of these challenges and therefore increase access to evidence-based psychological treatments [20, 21]. This is of great importance, especially considering the expected increase in demand for mental health care in the forthcoming years and limited healthcare resources [22–24]. In addition, important barriers for students to not seek help in case of future emotional problems appear to be stigma and preferring to solve problems alone. Hence, digital-delivered self-help interventions might especially be suitable for this particular young population that is reluctant to seek help [25].

Digital self-help interventions are delivered by internet, mobile device or computer and exist in guided and unguided forms. Digital interventions are not only promising due to young peoples’ increased usage of internet and mobile devices, but also because other potential benefits such as accessibility, reach, perceived anonymity and blended treatment where digital interventions are integrated into traditional treatment settings [24, 26–33]. Furthermore, digital alcohol moderation interventions might target people who are less likely to access traditional substance use facilities, such as women, young people and people who drink alcohol at problematic levels [34]. Young people also appear to already regularly use digital mental health services and their experiences with it are generally positive [35]. Notably, students seem to prefer digital treatment over face-to-face treatment for stigmatizing problems and anonymous alcohol interventions over formal alcohol resources such as talking to a doctor [36, 37]. Accordingly, an add-on digital alcohol moderation intervention to regular depression treatment may be an acceptable intervention for young adults with co-occurring depressive disorders and problematic alcohol use.

To date only a few randomized controlled trials (RCTs) have been conducted on evaluating digital interventions for co-occurring depressive disorders and problematic alcohol use. Contrary, various systematic reviews and meta-analyses have already shown that digital interventions, though mostly focused on only one condition, are effective in reducing depressive symptoms in youth [27, 38], adolescents [27], students [39, 40] and in adults [41, 42] and in reducing alcohol consumption among young adults [43], students [44] and adults [45–47]. A few meta-analytic studies have been conducted on digital interventions for co-occurring depressive disorders and problematic alcohol use. A sub-group meta-analysis from 2014, restricted to exclusively MI/CBT-based interventions, showed digital MI/CBT interventions may even reduce depression outcomes to a larger extent than face-to-face MI/CBT treatment in adults with co-occurring depression and problematic alcohol use [18]. Our recent systematic review with meta-analysis on digital interventions for co-occurring depression and problematic alcohol use also provides preliminary evidence of the small but significant positive effects of digital interventions on reducing depressive symptoms after 3-month follow-up (g = 0.34) and alcohol use after 6-month follow-up (g = 0.14) [48]. Digital interventions seem therefore particularly promising for this comorbid population. However, these meta-analytic findings are limited by high risk of bias ratings for all included studies, small amount of included studies with sometimes small sample sizes and differences with regards to digital intervention and population characteristics [48]. Furthermore, only two trials were conducted among younger populations and report mixed findings [49, 50]. Geisner et al. [49] found no effects for a brief web-based personalized feedback intervention on depression and alcohol outcomes among students with co-occurring problematic alcohol use and depressed mood. Deady et al. [50] evaluated a four-hour module web-based self-help for co-occurring depression and problematic alcohol use in young people aged 18–25 years. The authors found statistical significant effects in favour of the digital intervention compared to the control condition in depression and alcohol use outcomes post-treatment, but these group differences were not maintained after 3- and 6-months follow-up. Furthermore, no economic evaluations of digital interventions for co-occurring depressive disorders and problematic alcohol use have been conducted.

The previously discussed literature indicates that a digital alcohol moderation intervention might be a suitable and effective treatment for reducing depressive symptoms and alcohol use simultaneously among young adults with these co-occurring conditions. However, evidence on (cost-)effectiveness of digital interventions for young adults with these co-occurring conditions is insufficient. Therefore, we developed “Beating the Booze” (BtB) an add-on digital alcohol moderation adherence focussed guidance intervention as an adjunct to treatment as usual (TAU) for depressive disorders for young adults with co-occurring depressive disorders and problematic alcohol use. In the RCT presented in this protocol paper, we aim to evaluate the (cost-)effectiveness of this add-on digital alcohol intervention.

## Methods

This study protocol describes a multicentre RCT in which the (cost-) effectiveness of combining an add-on digital alcohol moderation intervention (BtB) with TAU will be compared to TAU alone. The target population comprises young adults (aged 18–35 years) with co-occurring depressive disorders and problematic alcohol use. We will evaluate alcohol use and depression outcomes. This protocol was written in accordance with the Standard Protocol Items: Recommendations for Interventional Trials (SPIRIT) guideline [51].

### Research aims

The primary outcome of the RCT is treatment response after 6-months follow-up. Treatment response is defined as a composite score that combines alcohol and depression outcome measures and indicates whether treatment has been successful or not. We expect to find a 25% treatment response in the control condition (TAU) and a 50% treatment response for the experimental condition (TAU + BtB). Previously conducted and ongoing trials indicate that changes in order of this magnitude can be achieved for combined digital alcohol and depression interventions [52, 53]. Furthermore, compared to participants in the control condition, we expect participants in the experimental condition to report a larger decrease in outcomes measuring alcohol use and depressive symptoms and a larger increase in quality of life.

### Design

We will conduct a pragmatic two-arm single-blind multicentre RCT with parallel-group design. Follow-up assessments will take place after 3 (T1), 6 (T2 and primary endpoint RCT) and 12 (T3) months post-randomization, see Fig. 1 for a flowchart of the study. The baseline and follow-up assessments are self-report measures and will be collected as online questionnaires. Where possible, we will use patient records to complement the self-reported data.

**Fig. 1 Fig1:**
[figure not shown]
Flowchart of study inclusion

### Economic evaluation

We will perform an economic evaluation alongside the RCT following a piggyback approach, to evaluate the cost-effectiveness of the intervention compared to care as usual. The economic evaluation will be performed in line with the International Society for Pharmacoeconomics and Outcomes Research (ISPOR) guidelines [54].

### Ethical approval

The research protocol was submitted to and approved by the Medical Research Ethics Committees United (MEC-U) in the Netherlands (NL66899.100.18). The research will be conducted in accordance with the Helsinki declaration and is pre-registered at the Netherlands Trial Register under registration number NL8122 (https://www.trialregister.nl/trial/8122) [55]. All adverse events reported spontaneously by the subject or observed by a member of the research team will be recorded. Any serious adverse events will be reported to the MEC-U. Written informed consent is obtained from all participants included in the study.

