#### Randomization and follow-up assessment

After completion of the baseline assessment, participants will be randomly allocated to the experimental or control group in a 1:1 ratio. Randomization will be performed using Castor EDC, a clinical data management system [58]. Using variable block randomization with block sizes of 2 and 4, randomization will be stratified for every participating site and for the group of participants recruited through social media. The randomization sequence is concealed for all members of the research team.

Castor EDC will be used for sending and storage of all online assessments [58]. All follow-up assessments will be online self-report questionnaires after 3, 6 (RCT primary endpoint) and 12 months post-randomization. Participants are e-mailed a link to the online questionnaires which they can fill-out on their mobile device (e.g. smartphone, computer or tablet). Participants who do not complete an assessment within 4 days will receive a reminder via e-mail. Participants who have not completed the assessments after the reminder, will be contacted by a research team member who motivates them and can assist them with possible assessment problems. If necessary, online assessments can also be completed by telephone. Research team members involved in follow-up assessments will be blinded to participants treatment allocation. Participants will receive a gift card with a value of €20 for each completed follow-up measurement assessment.

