#### Guidance

BtB includes a minimal level of asynchronously delivered adherence-focussed (i.e. not care-related) guidance from a “coach”. Guidance is performed by a member of the research team. Participants can also initiate contact with the coach by sending a message within the self-help environment. Guidance will be facilitative in nature, that means that it will be focused on increasing program adherence by answering any (technical) program related questions and motivating and reminding people to log in after a certain time of inactivity. The guidance will be tailored to the activity level of the participant, meaning that participants with low level of activity in the program will receive more reminders than participants who frequently log in to the program.

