#### Other variables of interest

Various other variables will be assessed. See Table 2 for an overview of all measurement instruments and assessment timepoints.
*Socio-demographic information:* General patient characteristics will be collected at baseline, these include: gender, age, marital status, employment status, education level and ethnicity.*Drinking motives:* Motives for drinking alcohol will be assessed with the Drinking Motives Questionnaire Revised (DMQ-R) [73]. The DMQ-R is widely used for assessing drinking motives among young populations. The 20-item questionnaire assesses motives for drinking on four factors: enhancing (e.g. drinking because it is fun) coping (e.g. drinking to forget worries), confirmative (e.g. drinking to be liked) and social motives (e.g. drinking to be sociable) [74]. The DMQ-R has shown to be acceptable for measuring drinking motives in adults with mood and anxiety disorders and appropriate for Dutch general adult population [74, 75].*General Mental Health:* General mental health is measured with the brief 5-item Mental Health Inventory (MHI-5) [76]. The MHI-5 is a subscale from the MOS SF-36 and has shown to be a good screener for mood disorders in the general population [77].*Patient satisfaction:* Participants’ treatment satisfaction is measured with a Dutch version of the 8-item Zufriedenheid (ZUF-8) questionnaire, scores range between 8 and 32, higher scores indicate more satisfaction with the received treatment [78, 79].*Intervention uptake:* Intervention uptake is measured through log data from the digital alcohol moderation intervention, for example by the number of times participants logged in, the number of completed modules and program duration.*Healthcare utilisation and productivity costs:* Assessment of healthcare costs and productivity losses or gains will be measured with the TIC-P (Trimbos/iMTA questionnaire on Costs associated with Psychiatric illness) a reliable instrument for collecting health care utilization and productivity loss [80].*Anxiety symptoms:* Anxiety symptoms will be measured with the brief 7-item Generalized Anxiety Disorder (GAD-7). Total scores range from 0 to 21, higher scores indicate a higher level of anxiety severity, cut-off points of 5, 10 and 15 indicate levels of mild, moderate and severe levels of anxiety respectively [81]. A meta-analysis has found the GAD-7 to be accurate in identifying generalized anxiety disorder and also any anxiety disorder, with high sensitivity and specificity values when using a cut-off point of 8 [82].*Traumatic events and post-traumatic stress symptoms:* Traumatic events and post-traumatic stress symptoms are assessed with the Dutch Childhood Trauma Questionnaire – Short Form (CTQ-SF) and Post-traumatic Stress Disorder Checklist for DSM-5 (PCL-5) [83, 84]. The CTQ-SF is a 28-item questionnaire that assesses five dimensions of childhood maltreatment: physical abuse, emotional abuse, sexual abuse, physical neglect and emotional neglect [85]. The Dutch CTQ-SF has been found to have adequate internal consistency and reliability. The 20-item PCL-5 questionnaire is widely used to screen for symptoms of post-traumatic stress disorder in the past month [86]. Several studies have found that the PCL-5 has good psychometric properties [84, 86]*Emotion dysregulation:* The widely used Difficulties in Emotion Regulation Scale (DERS-18) will be used to assess difficulties in emotion dysregulation [87]. The DERS-18 is an 18-item short form and has shown good internal consistency and convergent validity in populations with emotional disorders [87].*Resilience:* Psychological resilience will be measured with the brief Dutch 9-item Resilience Evaluation Scale (RES). The RES measures two constructs underlying resilience, that is self-confidence and self-efficacy. The instrument is used in various studies and has shown good psychometric properties [88].*Borderline personality features:* The 24-item Personality Assessment Inventory-Borderline Features (PAI-BOR) scale will be used to assess borderline features. The PAI-BOR questionnaire screens for borderline personality disorder features [89].*Perceived impact of COVID-19 measures:* We used a self-constructed 7-item questionnaire to assess the impact of COVID-19 and related measures on the participants’ depressive symptoms, alcohol use and study participation. The questions assess to what extent the pandemic led to either an increase, decrease or had no impact on depressive symptoms and alcohol consmption and what the reasons for the in-or decrease were. One question assessed whether the pandemic and restricting measures had an influence on any attempts of reducing alcohol use. Lastly, two questions assessed whether the pandemic had any influence on study participation and if so, for which reasons.

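### Adverse events are found passively and only the app arm has an added two-way channel to the research team, so the opportunity to detect them differs by arm

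*Protocol article*

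**What the plan says.** The protocol article describes how adverse events are found in one sentence, under Ethical approval: "All adverse events reported spontaneously by the subject or observed by a member of the research team will be recorded". The next sentence adds "Any serious adverse events will be reported to the MEC-U". No separate way of finding serious events is given. Other variables of interest and Table 2 list the instruments and their timing, and neither includes an adverse-event item.

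The Guidance section describes contact that exists only in the experimental arm. "Guidance is performed by a member of the research team", and the reminders follow activity: "participants with low level of activity in the program will receive more reminders than participants who frequently log in to the program". Contact also runs the other way: "Participants can also initiate contact with the coach by sending a message within the self-help environment". The control arm receives treatment as usual without the app or the coach.

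Contact common to both arms is described under Randomization and follow-up assessment: "All follow-up assessments will be online self-report questionnaires after 3, 6 (RCT primary endpoint) and 12 months post-randomization". Those who have not answered within 4 days get an e-mail reminder. A team member contacts those who still do not respond, and the forms can be completed by telephone if needed.

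**The concern.** When events are recorded because somebody mentions or notices them, the number recorded depends on how often participants are in touch with the people who record. Here the coach belongs to the research team, so anything a participant tells the coach counts as reported to, or observed by, that team. A participant who explains a period of inactivity may mention an admission or a crisis. A control participant with the same experience has no equivalent occasion.

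Two uses of the data are affected. Serious events reach the ethics committee only once the team knows of them, so those in control participants are more likely to be missed. And any harms table by arm that is eventually published would mix true differences with differences in detection. The Background section links this combination of conditions to a higher risk of suicide attempts, and the Discussion foresees implementation if the app proves effective, so an interpretable account of harms would be useful. The primary outcome, the sample size and the economic evaluation are not touched.

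**Working it through.** **Step 1: compare the routes to the research team by arm.**

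| Route | App arm | Control arm | Source (section) |
|---|---|---|---|
| Messages to a coach who is a team member | Yes | No | Guidance |
| Coach reminders, more with low activity | Yes | No | Guidance |
| Online questionnaires at 3, 6 and 12 months, without an adverse-event item | Yes | Yes | Randomization and follow-up assessment; Table 2 |
| Personal contact with non-responders; telephone completion | Yes | Yes | Randomization and follow-up assessment |
| Team contact details, given to social media recruits before allocation | Yes | Yes | Recruitment |
| Patient records where possible, to complement self-report | Yes | Yes | Design |
| TIC-P on care use at baseline and all follow-ups | Yes | Yes | Other variables of interest; Table 2 |

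The last five rows do not differ by arm. The first two do, and both can only add occasions for an event to become known. Follow-up staff are blinded, whereas a coach necessarily knows that the participant is in the app arm, so the extra route is also unblinded. No route is stated by which treating therapists pass events to the team.

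**Step 2: arm size.** The Sample size section gives a total of 156 for 50% against 25% response, two-sided alpha 0.05 and power 0.80. With the arcsine effect size, h = 2·arcsin(√0.50) − 2·arcsin(√0.25) = 0.5236. Then n = 2·((1.960 + 0.842)/0.5236)² = 57.26, or 58 per arm. 116 × 1.35 = 156.6, which agrees with the stated 156. Allocation is 1:1, so 156/2 = 78 per arm.

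**Step 3: what unequal capture would do.** The documents give neither event rates nor capture probabilities, so everything here is assumed. Let the true risk p be the same in both arms, and let c be the probability that an event is recorded.

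- Expected number recorded = 78 × p × c
- Apparent risk ratio = c(app)/c(control), whatever p is
- Apparent risk difference = p × (c(app) − c(control))

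With p = 20%, true events per arm = 78 × 0.20 = 15.6.

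| c control | c app | Recorded, control | Recorded, app | Ratio | Difference |
|---|---|---|---|---|---|
| 50% | 50% | 7.8 | 7.8 | 1.0 | 0 points |
| 50% | 60% | 7.8 | 9.4 | 1.2 | 2 points |
| 50% | 70% | 7.8 | 10.9 | 1.4 | 4 points |
| 50% | 80% | 7.8 | 12.5 | 1.6 | 6 points |
| 30% | 60% | 4.7 | 9.4 | 2.0 | 6 points |

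Over true risks of 10% to 30%, the spurious difference in the unequal rows runs from 0.10 × 0.10 = 1 point to 0.30 × 0.30 = 9 points. The ratio column is simply the assumed capture ratio, so the table shows the mechanism and does not estimate its size.

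**The case against.** The strongest reply is that one inclusive sentence under Ethical approval is being read as a complete procedure. It says which events will be recorded; it does not say that no others will be. A journal article commonly leaves adverse-event procedures to the full protocol, which is not shown. Observation by the team could also cover patient records and TIC-P answers, which exist for both arms. Control participants are not cut off, since shared contact routes exist. The guidance is described as minimal, asynchronous and not care-related, so it may yield few reports. Finally, safety is not among the stated aims or outcomes, and no analysis by arm is planned for it.

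Much of this stands. A reader might infer that events count only if volunteered or noticed, that serious control-arm events will go unseen, or that the trial cannot say whether the app is safe. The text supports none of these: the word only does not appear, shared routes exist, and the safety comparison is not one that the protocol sets out to make. Nor does it support an apparent doubling of harms, which appears only if twofold capture is assumed.

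One part does not fall. The article states a method, the method is passive, and the added channel is in one arm. Shared routes reduce the imbalance but cannot cancel a route that only one arm has. The records and the TIC-P could help, but nothing in the text ties either to adverse events.

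**Conclusion.** The point holds in a limited form. Under the capture method as stated, the opportunity to detect adverse events is unequal by arm, and the likely direction is more recorded events in the app arm. What is shown is unequal opportunity, not an observed imbalance. The size cannot be computed from the documents; the ratios of 1.2 to 2.0 rest wholly on assumed capture rates. The direction rests on one assumption, that some participants mention events to the coach which they would not otherwise report. The consequence is confined to the reporting of serious events to the ethics committee and to any harms table that is published. This is an inexpensive improvement, not a threat to the trial's main result.

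**What to change.** 1. Add one identically worded adverse-event question, including hospital admission, to the remaining online questionnaires at T1, T2 and T3 in both arms.
2. Screen the TIC-P answers for admissions. The protocol calls it "a reliable instrument for collecting health care utilization and productivity loss", and Table 2 schedules it in both arms at every follow-up. This assumes that the version in use asks about admissions, which should be checked.
3. Base any summary of harms by arm on these two sources, and list coach-detected and spontaneously reported events separately.

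The cost is one item in existing forms, a notification to the ethics committee and somewhat more events to process. The COVID-19 pandemic section says that data collection had partly taken place, so the new question reaches only follow-ups still to come. The TIC-P screen can be applied to all of them. The sample size, the primary outcome and the care of participants do not change.
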